## Procedure

### Recruitment and inclusion

Participants will be recruited at the Department of Neurosurgery or Orthopedics of the participating hospitals. The surgeons will screen the participants’ eligibility based on the information that was addressed in the standard anamnestic interview by the neurosurgeon or orthopedic surgeon. When the screening details are not fully known before inclusion, participants’ consent will be requested to ask him/her study-related information to complete the screening.

Before signing the informed consent form, a research assistant will extensively and verbally explain the study protocol. Next, the next study visits will be scheduled, and the participant is requested to indicate in which language (Dutch, English, or French) (s)he wishes to complete the questionnaires and perform the computer task. In addition, participants may also decide to complete the questionnaires of follow-up measurements online or on paper.

### Measurements

For an overview of the measured variables during each assessment, see Table 1.

**Table 1 Tab1:** Variables measured during each assessment

	Pre-surgery	Immediately after surgery	6 weeks post-surgery	3 months post-surgery	6 months post-surgery	12 months post-surgery
**Outcome variables**						
Self-reported work resumption			✓	✓	✓	✓
Self-reported pain severity	✓	✓	✓	✓	✓	✓
Self-reported disability	✓	✓	✓	✓	✓	✓
Self-reported quality of life	✓	✓	✓	✓	✓	✓
**Predictor variable**						
Self-reported fear of movement-related pain	✓	✓				
Self-reported avoidance behavior	✓	✓				
Generalization of fear of movement-related pain and avoidance behavior (assessed using the computer task)	✓					
Self-reported predictors of long-term disability and failure to return to work (yellow flags)	✓	✓				
Self-reported expectancies towards recovery and work resumption	✓	✓				
**Potential confounding variables**						
Demographic factors - Age - Sex - Relationship status - Highest grade or level of education completed - Duration of incapacity from work	✓					
- Work characteristics (e.g. employment status and rate)	✓		✓	✓	✓	✓
Self-reported work-specific characteristics - Emotional workload - Mental workload - Physical effort - Relationship with supervisor - Relationship with colleagues - Work pleasure - Career opportunities - Organizational commitment - Changing jobs		✓				
Surgery variables (complications during and after surgery)		✓				
Potential influence of COVID-19 - Presence of symptoms - Concerns about health - Physical inactivity	✓					
**Potential moderator variables**						
Self-reported intolerance of uncertainty	✓	✓				
Self-reported optimism	✓	✓				

#### Preoperative measurement

Prior to surgery, the predictor variables, the baseline of the outcome variables, and a selection of potential confounders will be assessed. Therefore, participants will be asked to complete a short computer task and several self-report questionnaires regarding fear of movement-related pain, avoidance behavior, the duration and severity of the pain before the surgery, their expectancies towards recovery and work resumption, optimism, yellow flags for long-term disability and failure to return to work, disability, quality of life, possible influence of the COVID-19 pandemic, and intolerance of uncertainty. We will also administer demographic variables (i.e., age, sex, relationship status, educational attainment, general work characteristics before incapacitated for work, and after work resumption, and start date of incapacity from work). The questionnaires will be implemented in Research Electronic Data Capture (REDCap), a secure web-based software platform [79, 80] and will be completed online on a laptop.

#### Postoperative measurement

In the week after the surgery, the predictor variables, the baseline of the outcome variables after the surgery, and the more specific work characteristics (e.g., workload, relationship with colleagues/supervisor, and pleasure in work) will be assessed. Participants will be asked to complete several self-report questionnaires to assess intolerance of uncertainty, fear of movement-related pain, avoidance behavior, expectancies towards their recovery and resumption of work, optimism, yellow flags for long-term disability and failure to return to work, pain severity, disability, quality of life, and work characteristics. The presence of unexpected complications that occurred during and/or after the surgery will be checked in the medical record of the participants. This measurement will take place during the participant’s recovery time in the hospital. The questionnaires will be implemented in REDCap and will be completed online on a laptop.

### Follow-up measurements: 6 weeks, 3 months, 6 months, and 12 months post-surgery

During the last four measurements, the outcome variables will be assessed. Six weeks, 3 months, 6 months and 12 months post-surgery, the research assistant will contact the participants by e-mail and/or telephone and ask them once again to complete some questionnaires regarding the outcome variables (i.e., sustainable work resumption, pain severity, disability, and quality of life), at home. Participants who experience difficulties completing the questionnaires independently can also complete them with telephone or online support of the research assistant (to prevent drop-out).

## Measurement instruments

### Outcome variables

#### Self-reported work resumption

To measure work resumption, we make a distinction between being fit for work, work resumption, and sustainable work resumption. Being fit for work will be operationalized by not receiving disability benefits. Work resumption will be operationalized by being at work without receiving disability benefits (on a dichotomous scale), and by time to relapse. Time to relapse is defined as the duration of being at work until a participant is on sick leave again. Sustainable work resumption will be operationalized by being at work for at least three consecutive months without receiving disability benefits (on a dichotomous scale). In addition, the duration of work resumption will be measured (on a continuous scale). All these variables will be assessed using custom-made self-report questions. The custom-made questionnaires are presented in Additional file 1. In order to calculate the time to relapse and sustainable work resumption, we will ask the participants to indicate when they were incapacitated from work and when they resumed work. In addition, we will directly ask if the participant resumed work for at least three consecutive months.

#### Self-reported pain severity

Pain severity will be operationalized as the intensity of the pain and will be assessed by one question of the short ÖMPSQ [75]. Participants are requested to answer this item (i.e. *How would you rate the pain that you have had during the past week?*) on a numerical rating scale with labels from 0 = *no pain* to 10 = *pain as bad as it could be*. The score on this item will be used as a measure of pain severity before and immediately after the surgery (as baseline measures) and 6 weeks, 3 months, 6 months, and 12 months post-surgery.

#### Self-reported disability

Disability will be operationalized as the degree to which pain interferes with daily functioning, and will be assessed by the Pain Disability Index (PDI) questionnaire [81]. The PDI is a self-report questionnaire that measures the degree to which pain interferes with functioning in seven areas: i.e., family/home responsibilities, recreation, social activity, occupation, sexual behavior, self-care, and life-support activity [82]. Ratings for each item range from 0 = *no disability* to 5 = *total disability*. A total score will be calculated as a reliable and valid [82] measure of the degree of disability before and immediately after the surgery (as baseline measures) and 6 weeks, 3 months, 6 months, and 12 months post-surgery.

#### Self-reported quality of life

Quality of life will be operationalized as satisfaction with life. It will be measured by the one item of the Riverside Life Satisfaction Scale (RLSS) with the highest factor loading [83]. Participants are requested to answer this item (*I am satisfied with my life overall*) on a 7-point Likert scale ranging from *strongly disagree* to *strongly agree*.

### Predictor variables

#### Self-reported fear of movement-related pain

To measure perceived harmfulness of movements, the following three photographs of the Photograph Series of Daily Activities-short electronic version (PHODA-SeV) [84, 85] were selected: (1) the photograph with the overall highest pain rating (i.e. shoveling soil with a bent back), (2) the photograph with the overall lowest pain rating (i.e. walking through the forest), and (3) the photograph with the highest variance (i.e. trampoline jumping). While a photo is presented on the screen, the participants are asked to rate (on a scale from 0 = *not harmful at all* to 100 = *extremely harmful*) to what extent they feel that the movement on the depicted photo would be harmful to their back if they were to perform it. If there is evidence that the three photographs sufficiently correlate, overall perceived harmfulness will be measured by calculating the average score of the three photographs. Otherwise, the individual score on every photograph will be used as a measure of relative perceived harmfulness.

#### Self-reported avoidance behavior

Avoidance behavior is defined as “*any act or series of actions that enables an individual to avoid or anticipate unpleasant or painful situations, stimuli, or events, including conditioned aversive stimuli”* [86]. In the current study, we will focus on pain-related avoidance behavior, i.e. the tendency to avoid stimuli or activities that could cause pain or pain-related complaints. It will be assessed by the Escape and Avoidance subscale of the short form of the Pain Anxiety Symptoms Scale (PASS-20) [87]. This subscale consists of five items considering thoughts or activities related to avoidance behavior, on which the participants are requested to indicate how often they engage in each of them (on a frequency scale with labels from 0 = *never* to 4 = *always*), and proved to be a valid measure of avoidance behavior [88, 89].

#### Generalization of fear and avoidance behavior

Generalization occurs when novel stimuli (generalization stimuli) evoke responses or behaviors similar to those elicited by a stimulus that naturally evokes a response or behavior (an unconditioned stimulus), or a stimulus that evokes a response or behavior because of its learned association with the unconditioned response (a conditioned response) (Hughes 2011). Such spreading of fear stimuli is following a “better safe than sorry strategy”, which is, in essence, adaptive, but can become maladaptive when there is no threat. Imagine someone experiencing pain when picking up grocery bags. Generalization occurs when the individual starts avoiding putting on pants and mopping the floor, even though these activities were not followed by pain in the past. Generalization, or the spreading of fear, and (generalized) avoidant decision-making to novel movements will be assessed by a recently developed computer task. After approval of the Social and Societal Ethics Committee (SMEC) of KU Leuven (registration number: G- 2018 07 1293) and the Ethical Review Committee Psychology and Neuroscience (ERCPN) of Maastricht University (registration number: Master_189_08_03_2018), this noninvasive computer task was validated in healthy participants at both KU Leuven and Maastricht University. Supporting (cross-site) evidence was found for the construct validity of the paradigm [90]. In this computer task, participants will view digitized images of a person moving in two postures. One posture will be paired with a neutral facial expression and the other posture with a loud human scream and a painful facial expression. Participants will be requested to indicate to what extent they expect the postures to induce pain in the depicted person, and to retrospectively rate their fear towards the postures. Generalization will be tested to intermediate postures (the generalization stimuli) that have a variable similarity between the original two postures, and by assessing pain-expectancy, fear of movement-related pain, and avoidance behavior to the novel stimuli. Pain-expectancy and fear of movement-related pain will be assessed for each stimulus type per block on a continuous rating scale (0–100) ranging from *not at all* to *very much*. Avoidance responses will be calculated as the mean percentage of trials in which participants avoided the painful outcome, for each stimulus type per block.

In contrast to the self-report questionnaires that need introspection from the participant and assess fear and avoidance as a cognitive representation, the computer task assesses fear and avoidance on a behavioral, observable level, is contextualized, and is likely more ecologically valid (being afraid of, and avoid a specific posture because they learned it was aversive). In addition, the computer task also measure generalization (spreading) of fear and avoidance, which is considered a unique predictor of negative outcomes (e.g., [52]). Therefore, we consider both measures complementary.

#### Self-reported predictors of long-term disability and failure to return to work (yellow flags)

Predictors of long-term disability and failure to return to work will be assessed by the short version of the ÖMPSQ [75]. The short version of the ÖMPSQ is a risk assessment tool that consists of 10 items that are scored on a verbal scale, or a numerical rating scale ranging from 0 to 10 (with different labels). This risk assessment tool addresses, among other things, the duration of pain before surgery, pain severity before and after surgery, and expectancies towards recovery and work resumption. The short version of the ÖMPSQ showed to be an accurate and predictive screening tool [75]. A total score will be calculated as a measure of estimated risk for future work disability.

#### Self-reported expectancies towards recovery and work resumption

Participants’ expectancies towards recovery and work resumption will, in addition to the questions of the short form of the ÖMPSQ, be assessed by custom-made self-report questions. We will assess (a) expectancy towards the duration of the pain*,* (b) expectancy towards the severity of the pain, (c) certainty about a decrease in pain, (d) expectancy about the severity of pain after surgery, (e) expectancy about the severity of pain 6 weeks after surgery, (f) expectancy about the severity of pain 3 months post-surgery, (g) expectancy about the severity of pain 6 months post-surgery, (h) expectancy towards resumption of work, (i) expectancy towards the duration until they are able to resume work, (j) certainty about their ability to resume work, (k) expectancy towards sustainability of work resumption. All these items will be rated on a numeric rating scale from 0 to 10 (with different labels). If the participant expects that (s)he will not be able to (sustainably) resume work after surgery, the underlying reason will be interrogated.

### Potential confounding variables

#### Demographic variables

We will register age, sex, relationship status, highest grade or level of education completed, the start date of their incapacity for work, and work characteristics (e.g. type of work, type of contract, and employment rate/hours) before being incapacitated for work and after work resumption. Based on the start date of incapacity for work and the date of work resumption, we will calculate the duration of incapacity for work before surgery. We include this as a potential confounder because a study of Du Bois (2014) showed that 70% of the individuals who were incapacitated for work for longer than 3 months before surgery were unable to resume work 1 year after surgery.

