### Participants

Three hundred individuals with radicular pain will be recruited. Every participant will be planned for back surgery in one of the nine involved Belgian hospitals (i.e., University Hospitals Leuven, Ziekenhuis Oost-Limburg, Noorderhart Mariaziekenhuis, AZ Groeninge, GasthuisZusters Antwerp, Centre Hospitalier de Wallonie picarde, Imeldaziekenhuis, Regional Hospital Heilig Hart Tienen, and AZ Sint-Lucas Ghent). Inclusion criteria are: (a) age between 18 and 55, (b) proper mastery of the Dutch, English, and/or French language, (c) intermittent or constant invalidating lumbosciatica for less than 1 year prior to the planned surgery, operationalized by being on sick leave on the day of the surgery (documented by the surgeon), (d) radicular pain in the leg(s) due to compression, that will be treated surgically by performing a decompression without it leading to fusion and/or fixation, and (e) self-employed or has an employment contract, and is on sick leave for less than 1 year at the day of the surgery. Reasons for exclusion are (based on self-report): (a) being treated (ambulant or residential) for substance abuse, suicidal ideation, or a psychotic disorder in the year before the consult with the surgeon, (b) at least one back surgery in the last 5 years prior to the planned surgery, and (c) presence of a comorbid condition (e.g. a severe neurological deficit, a pulmonary embolism, permanent paralysis, and another pain problem in the limbs), which may affect the pain, the outcome of the surgery, the duration of the rehabilitation, and/or the participant’s capacity to return to work during the course of the study. At the end of the study, participants will receive a gift voucher worth of maximum 40 euros (at a rate of 10 euros per completed follow-up measurement).

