### Primary objectives

Logistic regressions will be performed to examine the effect of preoperative as well as postoperative fear of movement-related pain and avoidance behavior (and their generalization), expectancies towards recovery, expectancies towards work resumption, presence of yellow flags, on return to work at 6 weeks, 3 months, 6 months, and 12 months post-surgery. Next, a time-dependent Cox regression will be performed to examine the effect of the predictor variables on return to work over time. The same analyses will be conducted for the sustainability of work resumption at 3 months, 6 months, and 12 months post-surgery as a dependent variable.

Multiple linear regression analyses will be carried out to examine the effect of the predictor variables on the duration to resume work over time. Log-rank test and Kaplan–Meier plots will be applied to compare rates of work resumption between participants with different profiles (i.e. at work or not during the different measurement moments).

All interaction effects, including the predictor*time interactions, will be explored. Following potential confounders will be included as covariates in each analysis: age, sex, work characteristics, duration of incapacity for work, surgery complication, and the potential influence of the COVID-19 pandemic.

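### The confounder named as incapacity before surgery is calculated up to the date of work resumption, so taken literally it carries the outcome into the work-resumption models

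*Protocol article*

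**What the plan says.** Under Potential confounding variables, subsection Demographic variables, the article gives one rule for this covariate: "Based on the start date of incapacity for work and the date of work resumption, we will calculate the duration of incapacity". The same sentence goes on to name the interval as the one before surgery: "the date of work resumption, we will calculate the duration of incapacity for work before surgery". The reason given for including it is a cited study of people incapacitated for more than 3 months before their operation.

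Three other places bear on the definition:

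- Table 1 lists duration of incapacity among the demographic factors, ticked in the pre-surgery column only.
- Preoperative measurement lists the date to be collected at that visit: "and start date of incapacity from work". It mentions no resumption date for this purpose.
- Participants makes sick leave an entry condition: "operationalized by being on sick leave on the day of the surgery (documented by the surgeon". Sick leave must also have lasted less than 1 year by then.

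Primary objectives then states: "Following potential confounders will be included as covariates in each analysis: age, sex, work characteristics, duration of incapacity for work". The words before surgery do not reappear there. Secondary objectives repeats the list for pain severity, disability and quality of life.

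**The concern.** A confounder has to be fixed before the outcome period starts. An interval that ends at work resumption is not. It is known only once the outcome has occurred, and it grows one day for each day that return to work is delayed. Primary objectives models exactly that delay, as return to work at four time points, in a Cox regression and as the duration to resume work.

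If fear or avoidance delays return to work, part of the delay is already inside the covariate, and adjusting for it removes that part from the estimated effect. The primary hypothesis could then look weaker than it is because of how a covariate was coded. Someone who never resumes has no end date, so the covariate has no value for the group the study most wants to explain.

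**Working it through.** The article gives no figure for this covariate. Its one computed figure, n = 167, reproduces (noncentral F, numerator df 14, f² = 0.1494, power 0.902) but plays no part here.

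**Step 1: what the rule computes.** Let S be the start of incapacity, O the date of surgery and R the date of resumption. Everyone is on sick leave at O, so R falls after O for the current spell. Then

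R − S = (O − S) + (R − O) = P + T,

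where P is pre-surgery incapacity (under 12 months by eligibility) and T is post-surgery time to resumption. The name, Table 1, the preoperative visit and the rationale all describe P. Only the calculation rule gives P + T.

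**Step 2: effect in a linear model.** Write T = a + bX + e for predictor X, with P independent of X and e. Regressing T on X and D = P + T gives an X coefficient of

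b × Var(P) / [Var(P) + Var(e)].

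For SD(P)/SD(e) = 0.25, 0.5, 1, 1.5, 2 and 3, the retained share is 0.06, 0.20, 0.50, 0.69, 0.80 and 0.90. More than half is lost only when pre-surgery duration varies less than residual time to resumption.

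**Step 3: simulation.** Assumptions, none of them given in the article:

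- hazard ratio 0.7 per SD of X, with exponential T;
- P independent of X and T;
- non-resumers set to 12 months;
- 100,000 subjects (3,000 for Cox).

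Two resumption rates are anchored on the Back surgery section: about 20% not back at 12 months (hazard −ln 0.20/12 = 0.134 per month) or 82% back at 3 months (−ln 0.18/3 = 0.572 per month). A constant hazard cannot meet both; the second leaves under 1% not back at 12 months. The table shows the share of the X coefficient lost when P + T replaces P. The logistic column is the range over 1.5, 3, 6 and 12 months.

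| Pre-surgery sick leave (months) | Resumption | Linear | Cox | Logistic |
|---|---|---|---|---|
| uniform 0–3 | 20% not back at 12 | 96% | 85% | 39–85% |
| uniform 0–3 | 82% back at 3 | 82% | 64% | 45–75% |
| uniform 0–6 | 20% not back at 12 | 85% | 70% | 28–68% |
| uniform 0–6 | 82% back at 3 | 55% | 46% | 25–56% |
| uniform 0–12 | 20% not back at 12 | 58% | 40% | 17–47% |
| uniform 0–12 | 82% back at 3 | 23% | 14% | 10–32% |
| exponential, mean 2, capped at 12 | 20% not back at 12 | 81% | 69% | 30–73% |
| exponential, mean 2, capped at 12 | 82% back at 3 | 48% | 47% | 19–30% |

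Check of the first row against Step 2: Var(P) = 3²/12 = 0.75. The simulated SD of T is 4.25 and b is 1.219, so Var(e) = 4.25² − 1.219² = 16.58. The retained share is 0.75/17.33 = 0.04, a loss of 96%.

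**Step 4: undefined values.** If 20% never resume within a year, the covariate is undefined for 0.20 × 300 = 60 participants, or 0.20 × 150 = 30 if half have dropped out as Sample size allows.

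**The case against.** The strongest reply is that this is a slip in one clause and not the plan. The variable's name, its place in Table 1, the date collected preoperatively and the rationale all point to an interval ending at surgery. Self-reported work resumption separately uses incapacity and resumption dates to derive outcomes, so the sentence may simply have run two calculations together. This stands as a reading of intent, and it is why the point is put as a contradiction. It does not make the rule harmless: no other calculation is given, and the covariate list in Primary objectives drops the qualifier that would have corrected it.

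Four stronger readings are tempting, and the documents do not support them.

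- *The covariate removes most of the effect.* That needs the spread of pre-surgery sick leave and of time to resumption, and the article gives neither. Half of the scenarios above lose less than half of the effect in the Cox model.
- *The outcome sits inside every model.* In Secondary objectives the outcomes are pain severity, disability and quality of life. There P + T is a post-surgery variable that may lie on the causal path, but it does not contain those outcomes.
- *Non-resumers will be dropped.* The article states no complete-case rule and says that all included participants will be analysed. They would be lost only if cases with a missing covariate were excluded.
- *Work characteristics recorded after resumption are also adjusted for.* Demographic variables records them "before being incapacitated for work and after work resumption", and Table 1 repeats "Work characteristics (e.g. employment status and rate" at each follow-up. Primary objectives never says that the later values enter the models, and pre-incapacity values are recorded as well. This is an ambiguity, not an error.

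**Conclusion.** The definition is wrong as written and should be corrected. The stated calculation cannot produce the quantity it names, and followed literally it puts time to resumption on both sides of the work-resumption models. The bias is towards no effect. Its size is uncertain: about 10% to 96% of the coefficient across the scenarios, large when pre-surgery sick leave varies little compared with time to resumption and modest when it varies more. With the interval ended at surgery, this source of loss disappears. That range assumes that the predictor is unrelated to pre-surgery duration, that return-to-work times are exponential and that non-resumers are set to 12 months. The contradiction itself rests on none of these assumptions; it follows from the eligibility criterion and the wording of the rule. A reader should not conclude that the primary result is bound to be falsely negative, because the likely intent was the correct interval.

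**What to change.** In Demographic variables, define the covariate as the date of surgery minus the start date of the current incapacity, and state that the resumption date is used only to derive outcomes. Carry the words before surgery into the covariate lists in Primary objectives and Secondary objectives. As a minor clarification, state that work characteristics, when adjusted for in the work-resumption models, means the pre-incapacity values recorded before surgery.

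The cost is a few words in three places. The start date is already collected preoperatively and the date of surgery is necessarily known, so no new data are needed.
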